## Abstract

**Background:**

Public Speaking Anxiety (PSA) is a form of social anxiety spread among university students, negatively affecting both academic performance and overall psychological well-being. Virtual Reality (VR)–based interventions combined with Cognitive Behavioral Therapy (CBT) represent a promising approach for treating PSA, as they enable gradual and controlled exposure to feared social situations by simulating realistic audiences and environments. The primary aim of this study is to evaluate whether the use of VR as a support to standard psychotherapy is effective in managing anxiety and PSA in university students who access the University Psychological Counseling Service (UPCS).

**Methods:**

This article outlines the study protocol for a randomized controlled trial (RCT). Participants will be divided into two groups: (1) a control group receiving psychological counseling, and (2) an experimental group that receives psychological counseling integrated with VR interventions based on 360° video scenarios. The intervention will include two VR-based modules: a VR–Exposure and Response Prevention (ERP) module, designed to provide graded immersive exposure to anxiety-provoking scenarios, and a VR–Acceptance and Commitment Training (ACT) module, aimed at enhancing mindfulness and psychological flexibility through guided experiential practice. Psychological and physiological data collected during the sessions will be analyzed to compare the effectiveness of VR-integrated psychotherapy with traditional counseling alone.

**Discussion:**

This study will introduce a novel VR-based ERP and ACT training protocol designed to reduce public speaking anxiety in university students by integrating innovative, immersive VR scenarios within a psychological counseling context. The proposed approach may be particularly relevant for university settings, as it offers a scalable, standardized, and controllable VR-supported counseling protocol aimed at reducing PSA, enhancing students’ academic functioning (e.g., oral exams and presentations), and strengthening the overall effectiveness of university psychological counseling services.

**Trial registration:**

This protocol was registered at the Clinical Trials.gov (Identifier: NCT07351409) on January 16, 2026.

**Supplementary Information:**

The online version contains supplementary material available at 10.1186/s40359-026-04418-4.

## Introduction

In recent years, the rising prevalence of mental health difficulties among university students has emerged as a critical public health concern, prompting growing attention from researchers, higher-education institutions, and mental health services [1]. Recent epidemiological studies have shown that university students often report high levels of stress, generalized anxiety [2], and social anxiety [3]. Social anxiety disorder, particularly Public Speaking Anxiety (PSA), is highly prevalent among students worldwide, affecting over 60% in surveys across the USA, Brazil, and Finland [4]. This fear often emerges in adolescence, causing significant distress and physical symptoms, highlighting the need for interventions to reduce speaking-related anxiety, referred to as Public Speaking Anxiety (PSA). Multiple factors may contribute to increased anxiety among university students, including academic pressure, fear of failing exams, interpersonal difficulties, and the perceived need to succeed after graduation [5]. Providing students with effective support for managing their concerns and anxiety symptoms can promote both their personal well-being and their academic success. In this context, University Psychological Counseling Service (UPCS) gained a central role in responding to the growing demand for psychological and/or psychotherapeutic support, particularly during the pandemic and post-pandemic periods [6–8].

Among the psychotherapeutic approaches for anxiety, Cognitive Behavioral Therapy (CBT) has demonstrated robust empirical support and clinical efficacy [9]. First and second waves of CBT employ techniques such as systematic desensitization, applied relaxation, targeting the somatic symptoms of anxiety, as well as skills training and cognitive restructuring aimed at modifying dysfunctional thought patterns. The third-wave CBT models, such as Acceptance and Commitment Therapy (ACT), have expanded the therapeutic focus beyond symptom reduction to encompass core processes of psychological flexibility, by integrating mindfulness and acceptance principles to foster adaptation and resilience in the face of distressing experiences [2].

ACT is a process-based behavioral intervention that aims to enhance psychological flexibility, defined as the capacity to remain in conscious contact with the present moment while engaging in effective, values-guided action [10, 11]. The core processes underpinning ACT are acceptance, cognitive defusion, present-moment awareness, self-as-context, values clarification, and committed action. Within the context of public-speaking anxiety, ACT supports individuals in reducing defensive avoidance and in approaching performance-related cues with openness and behavioral willingness, thereby enabling more adaptive engagement with anxiety-eliciting situations [12].

Conducting exposure exercises for PSA during psychotherapy sessions has historically been challenging or even impractical, as it requires access to and control over a live audience [13]. Immersive Virtual Reality (IVR) technology can overcome this limitation by enabling safe, controllable, and repeatable virtual environments, in which social-evaluative stimuli, such as the presence of an audience in a classroom, can be systematically manipulated. These technologies can facilitate emotional regulation, behavioral change, and the integration of lived experiences by providing immersive, embodied, and repeatable simulations, thereby activating both cognitive and affective processing systems and fostering learning and desensitization in a realistic yet secure context [14, 15]. These possibilities allow us to overcome real setting limitations and lead to the development of Virtual Reality Exposure Therapy (VRET) for the treatment of PSA. Through VR-based exposure, the feared stimulus can be precisely controlled and gradually modulated. A growing body of empirical studies [16–19] demonstrated that VR-based exposure is associated with significant reductions in PSA symptoms, yielding clinical benefits often maintained over time. More recently, research has begun integrating VR with ACT-based practices. A randomized controlled trial [20] showed that a brief VR-based ACT intervention combining graded virtual exposure with ACT-consistent guidance (e.g., mindful noticing, acceptance, and cognitive defusion) resulted in a significant reduction in social and public speaking anxiety and increases in psychological flexibility among university students. These findings highlight the potential of VR not only as a vehicle for exposure but also as an effective platform for delivering ACT-consistent mechanisms of change in an immersive and experiential format.

Despite these advances, the literature on VR-based interventions for PSA and social anxiety remains limited by several methodological shortcomings. Studies rely primarily on self-report instruments, which mainly capture the subjective dimension of anxiety and provide limited insight into underlying physiological or behavioral processes [9, 13]. Moreover, VR-based interventions are rarely compared directly with established therapist-delivered interventions, making it difficult to determine whether the VR-based element offers added therapeutic value beyond traditional cognitive-behavioral approaches [4, 16]. A further limitation concerns the scarcity of long-term follow-up assessments, which restricts conclusions regarding the durability of treatment gains.

To extend the current knowledge and to test the efficacy of application-based VR interventions, the present experimental protocol is designed to overcome some of the methodological limitations previously identified in the literature. Within this framework, UPCS provides an optimal first-line intervention setting for implementing VR, offering access to a clinical environment in which immersive scenarios can be used to simulate feared social and public-speaking situations. This study is expected to contribute to addressing the current lack of evidence on CBT combined with 360° video–based VR exposure for PSA in university students and to provide preliminary support for a novel VR-based ERP and ACT protocol specifically tailored to a university counseling context.

## Method

### Aim

We adopt a two-arm randomized controlled trial (RCT) design to investigate whether VR-delivered controlled exposure can complement standard psychological counseling in addressing PSA and general anxiety symptoms among students accessing the UPCS. The findings are expected to provide evidence regarding the effectiveness of integrating VR-based exposure as an adjunct to Exposure and Response Prevention–Acceptance and Commitment Therapy (ERP-ACT) within counseling to manage anxiety and stress in university students.

It is hypothesized that:

Primary Outcome - Students receiving brief psychological counseling supported by ERP and ACT training combined with VR-based exposure exhibit significantly greater reductions in PSA and anxiety levels from baseline (T0) to post-intervention (T1), compared with students receiving standard psychological counseling alone.Secondary Outcome - The two VR components (ERP and ACT) are expected to exert differential effects. Specifically, the relaxation modules should primarily reduce physical tension and physiological arousal, whereas the immersive exposure modules should mainly target the psychological aspects of public speaking, leading to lower fear and reduced perceived mental effort during performance-related scenarios. Physiological data are continuously recorded during each intervention session to assess patterns of arousal and recovery and to examine whether VR-supported counseling is associated with different within-session responses compared with counseling alone.Other Pre-specified Outcome - These benefits are expected to be maintained over time; therefore, students in the VR-ERP and VR-ACT training conditions are expected to continue to exhibit better outcomes at the 3-months follow-up assessment (T2), compared with students receiving standard counseling alone.

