### Sample size

A priori sample-size estimation is conducted to determine the number of participants required to detect the expected effects of the VR-based exposure intervention on the primary outcome measures. Evidence from a systematic review [21], which examined virtual reality–based interventions targeting public-speaking anxiety in student populations, indicates that VR exposure procedures typically yield moderate-to-large reductions in anxiety symptoms compared with control or baseline conditions. Reported effects across the studies reviewed are consistent with the magnitude commonly observed in the broader VRET literature, supporting the assumption of a moderately large effect size for the planned between-group comparison.

Based on this evidence, we adopt an expected effect size of Cohen’s d = 0.75 for the between-group differences in change scores from baseline to post-intervention between the VR exposure and control groups. A power analysis conducted using G*Power 3.1 (two-tailed independent-measures t-test, α = 0.05, power = 0.80) indicated that 29 participants per group would be required to detect an effect of this magnitude.

To ensure adequate statistical power after accounting for participant attrition, commonly estimated at 15%-20% in VR-based intervention studies, we plan for an upper-bound dropout rate of 20%. Accordingly, the required number of participants is adjusted to 36 participants per group, resulting in a total target sample of 72 participants [22]. This sample size is expected to provide sufficient statistical sensitivity to detect clinically meaningful effects of the VR intervention while remaining feasible for a single-site randomized controlled trial.

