#### Psychological assessment

The protocol involves the assessment of participants through the administration of standardized self-report psychological tests designed to evaluate levels of public speaking anxiety and state and trait anxiety levels.

The instruments are:

The Italian version of the *Personal Report of Public Speaking Anxiety* (PRPSA) [23] is a self-report questionnaire designed to measure the level of anxiety individuals experience when speaking in public. The scale assesses multiple dimensions of public speaking anxiety, including cognitive, physiological, and behavioral components, capturing both anticipatory anxiety and anxiety during performance. The PRPSA consists of 34 items, each rated on a 5-point Likert scale (1 = strongly disagree to 5 = strongly agree). Items reflect feelings of tension, nervousness, and physiological arousal (e.g., “My hands tremble when I try to handle objects on the podium”), as well as negative self-appraisal and fear of audience evaluation. Total scores range from 34 to 170, with higher scores indicating greater levels of public speaking anxiety. Conventionally, scores above 131 suggest high anxiety, scores between 98 and 131 indicate moderate anxiety, and scores below 98 indicate low anxiety. The Italian version maintains strong psychometric properties, with high internal consistency (Cronbach’s α > 0.90) and good test–retest reliability. It has been validated for use among university students and adults, proving useful in both clinical and research contexts, examining performance-related social anxiety and communication apprehension.The Italian version of the *State-Trait Anxiety Inventory*,* Form Y* (STAI) [24, 25] was adopted to measure two distinct dimensions of anxiety: (i) State Anxiety (S-Anxiety), a temporary emotional condition characterized by feelings of tension, apprehension, and heightened autonomic nervous system activity, reflecting how the respondent feels at the present moment; and (ii) Trait Anxiety (T-Anxiety), a relatively stable disposition to perceive situations as threatening and to respond with anxiety across time and contexts. Each subscale consists of 20 items, rated on a 4-point Likert scale (ranging from 1 = almost never to 4 = almost always for trait anxiety, and 1 = not at all to 4 = very much so for state anxiety). Scores range from 20 to 80 for each subscale, with higher scores indicating greater anxiety levels. The Italian adaptation has demonstrated good psychometric properties, including high internal consistency (Cronbach’s α typically between 0.86 and 0.95) and construct validity consistent with the original instrument, making it one of the most widely used anxiety measures in both clinical and research settings in Italy.

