### Statistical analyses

All statistical analyses are conducted using IBM SPSS Statistics (version 29.0) and follow a pre-specified analytic strategy designed to evaluate changes in psychological and physiological outcomes across the study period and to compare the effectiveness of standard counseling with and without VR-based exposure. Descriptive statistics are first computed to characterize the sample to assess baseline equivalence between groups. Reliability analyses (Cronbach’s α and McDonald’s ω) are performed to confirm the internal consistency of the psychometric instruments.

Because the study involves repeated assessments at baseline (T0), post-intervention (T1), and follow-up (T2), the primary analyses use linear mixed-effects models, an approach well suited to handling longitudinal data and missing observations. These models test for the main effects of time and group, as well as the critical time × group interaction, indicating differential improvement between the VR-enhanced counseling condition and the control group. Where significant interactions emerge, post hoc comparisons with Bonferroni adjustment are conducted to identify specific temporal patterns of change. Complementary analyses of change scores (ΔT1–T0 and ΔT2–T0) are performed using independent-sample t-tests or, where assumptions are violated, Mann–Whitney U tests; General Linear Models including baseline variables and demographic covariates further clarify group differences in treatment response.

Physiological data collected during VR sessions (including heart rate, HRV, and electrodermal activity) are examined through mixed models and event-based analyses aligned with the structure of the VR exposure tasks, allowing evaluation of both arousal patterns and recovery processes. Exploratory regression models are used to identify predictors of treatment benefit, such as baseline symptom severity or physiological reactivity during VR exposure.

Missing data are handled through the mixed-model framework, which accommodates incomplete longitudinal data; if dropout shows non-random patterns, multiple imputation is applied as a sensitivity check. For all analyses, statistical significance is set at α = 0.05, with appropriate corrections for multiple comparisons.

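### The 80% power applies to one test on one measure, but the primary hypothesis joins public speaking anxiety and anxiety, and no scale is named as the single primary

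*Protocol article*

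**What the plan says.** - **Aim, primary hypothesis.** Students receiving counseling with VR are to "exhibit significantly greater reductions in PSA and anxiety levels from baseline (T0) to post-intervention (T1), compared with students receiving standard psychological counseling alone". The two constructs are joined by *and*.
- **Sample size, purpose.** The estimate is meant to give the number "required to detect the expected effects of the VR-based exposure intervention on the primary outcome measures". The measures are plural and not listed.
- **Sample size, calculation.** The authors adopt an "expected effect size of Cohen’s d = 0.75 for the between-group differences in change scores from baseline to post-intervention", not tied to any scale. A two-tailed independent t-test at α = 0.05 with power 0.80 "indicated that 29 participants per group would be required to detect an effect of this magnitude". A 20% dropout allowance raises this to 36 per group, 72 in total. The supporting review concerns VR interventions for public speaking anxiety in students.
- **Psychological assessment and Table 1.** The tests are "designed to evaluate levels of public speaking anxiety and state and trait anxiety levels". They are PRPSA, STAI-Y State and STAI-Y Trait, all given at enrolment, T1 and T2. None is ranked above the others.
- **Statistical analyses.** For all analyses, "statistical significance is set at α = 0.05, with appropriate corrections for multiple comparisons". The only correction named is Bonferroni, for post hoc comparisons after a significant time × group interaction.

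**The concern.** A power figure belongs to a success rule. Here the figure is for one comparison on one measure at the full 0.05, while the hypothesis it supports concerns PSA and anxiety together. If both must improve significantly, the chance of success is lower than for either alone. If each is tested at a reduced alpha, power per measure falls. If either may succeed at an uncorrected 0.05, the false-positive rate rises above 5%.

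Two things are at stake: whether 72 participants are enough for the claim the trial intends to make, and what counts as a positive trial. With no designated primary, a result on any one scale, or any combination, could later be presented as meeting the primary hypothesis.

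**Working it through.** **Inputs.** From Sample size: d = 0.75 on change scores, two-sided α = 0.05, power 0.80, 29 evaluable per group, 20% dropout. Assumed here, because the protocol is silent: the same d applies to every primary measure, and the correlation between measures lies from 0 to 0.9.

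**Step 1: reproduce the plan's figure.** Two-sample t-test, n per group, df = 2n − 2, noncentrality δ = d·√(n/2). For n = 29: δ = 0.75 × √14.5 = 2.856, df = 56, critical value 2.003. Noncentral-t power = **80.1%** (78.7% at n = 28). The stated 29 is right for one test. Dropout: 29/0.80 = 36.25. The plan uses 36, where rounding up gives 37; this is immaterial here.

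**Step 2: Bonferroni over the primary measures, power per measure at n = 29.** δ is still 2.856 and only the critical value changes.

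| Primary measures | α per test | Critical value | Power per measure | Evaluable n per group for 80% | After 20% dropout |
|---|---|---|---|---|---|
| 1 | 0.05 | 2.003 | 80.1% | 29 | 36 (plan) |
| 2 | 0.025 | 2.303 | 70.9% | 36 | 36/0.8 = 45 (90 in total) |
| 3 | 0.0167 | 2.468 | 65.1% | 39 | 39/0.8 = 48.75, so 49 (98 in total) |

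**Step 3: every measure must be significant, each at 0.05.** No alpha correction is needed. With independent measures, joint power is 0.801² = 0.64 for two and 0.801³ = 0.51 for three. Simulation of correlated normal outcomes, n = 29 per group:

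| Correlation | 0 | 0.3 | 0.5 | 0.7 | 0.9 |
|---|---|---|---|---|---|
| Two measures | 64% | 67% | 69% | 71% | 75% |
| Three measures | 52% | 57% | 61% | 66% | 72% |

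(The simulated 52% and the product 51% for three independent measures are both rounded from 51.5%.) Reaching 80% would take about 35–38 evaluable per group for two measures and 38–43 for three, at correlations from 0.7 down to 0.

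**Step 4: at least one measure significant after Bonferroni, n = 29.**

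| Correlation | 0 | 0.3 | 0.5 | 0.7 | 0.9 |
|---|---|---|---|---|---|
| Two measures | 92% | 88% | 85% | 82% | 77% |
| Three measures | 96% | 91% | 87% | 82% | 75% |

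Familywise error stays at about 5% or below.

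**Step 5: at least one measure significant with no correction.** For independent measures the false-positive rate is 1 − 0.95² = 9.75% (two) and 1 − 0.95³ = 14.3% (three). At correlation 0.9, simulation gives about 7% and 8%. The ranges are therefore about 7–10% and 8–14%.

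**The case against.** - **Some success rules do reach 80%.** A reader might infer that no rule gives both 5% error and 80% power. That is not so: Step 4 shows that at least one success after Bonferroni gives about 82–96% at correlations up to 0.7. But the protocol states no such rule, and its hypothesis says *and*, not *or*.
- **Three primaries are not stated.** The Aim names two constructs, and the scales are only listed and scheduled elsewhere. This stands, so the three-measure figures are conditional. The shortfall is already present with two.
- **The promised correction may not concern the primary measures.** Also true. Bonferroni is named only for post hoc time comparisons, and the closing sentence on corrections does not say where they apply. A reader might infer either that the plan will test several primaries uncorrected or that it has committed to splitting alpha across them. The text supports neither.
- **Correction details belong in a SAP.** Agreed, and their absence is not the point. What this document does state, a hypothesis on more than one construct and a calculation for one test, does not match.
- **All 36 per group might be evaluable.** Then Bonferroni power would be 81% (two) or 77% (three) per measure. But the plan itself allows for 20% loss.
- **The trial calls its evidence preliminary.** That lowers the stakes, but the protocol still claims adequate power after attrition.

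A reader might also infer that d = 0.75 cannot hold for trait anxiety because the protocol describes it as a stable disposition. The document gives no effect size for any single scale, so nothing here rests on that.

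**Conclusion.** The concern holds in this form: 29 per group is correctly computed for one measure tested once at 0.05, but the primary hypothesis spans at least two constructs and no single primary scale is named. Read literally, with both PSA and anxiety having to improve, power is about 64–75% instead of 80%. With Bonferroni over two measures it is about 71% per measure. If all three scales are taken as primary, the figures are about 51–72% jointly or 65% per measure.

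These figures assume 29 completers per group, d = 0.75 on every measure and correlations of 0 to 0.9. A smaller effect on any measure would lower joint power further. An inflated false-positive rate is a risk only if any one measure may succeed without correction across measures, which the protocol neither adopts nor clearly excludes.

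**What to change.** Name the PRPSA change from T0 to T1 as the single primary outcome in the Aim, Sample size and Statistical analyses sections. It is the scale closest to the public-speaking-anxiety evidence behind the assumed effect, and the 29-per-group calculation then matches the primary claim. Make STAI-State and STAI-Trait secondary, tested in a stated fixed order only if PRPSA is significant.

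If several primaries are kept, list them, state the success rule (all, each with adjusted alpha, or at least one with adjusted alpha), and restate the power or the sample size from the tables above. For example, Bonferroni at 80% per measure needs 90 participants in total for two measures or 98 for three, against the planned 72.

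The first option costs a protocol amendment and matching registry wording, with no extra participants. Its small downside is that the STAI results become secondary.
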